### Outcome measures

The following primary outcome measures are being utilised:

▪ Number of falls (mean per patient per month)

▪ Potentially inappropriate prescribing (number of drugs which match the STOPP criteria [28] at each data collection point).

Secondary outcome measures include:

▪ Medication costs (mean drug costs per patient - net ingredient costs for 28 days)

▪ Utilisation of primary care, secondary care and personal social services health professional time (GP, nurse and other)

▪ Emergency hospital admissions and Accident and Emergency (A&E) visits (number of admissions in six months per patient)

▪ Mortality.

### Support for the trial

In terms of infrastructure to support the trial and ensure its completion, there are a number of mechanisms in place. In the first instance, the trial is supported by input from a multi-disciplinary research team. In addition to the Principal Investigator (PI), study coordinator and senior pharmacists from the MMT, the team is comprised of specialists in trial design, pharmacy practice, statistics and health economics.

A Management Group will meet on a quarterly basis throughout the duration of the trial. The Management Group consists of the members of the research team, a local GP representative, a community geriatrician, a falls specialist, care home representative and two lay members. The purpose of the Management Group is to set objectives, agree timelines, monitor progress and facilitate study delivery and evaluation.

The study also has a Trial Steering Committee to provide overall supervision of the trial, with an emphasis on trial progress, adherence to protocols, consideration of new information pertinent to the trial, data monitoring, reporting and ethical issues. The Steering Committee is chaired by a statistician and has care home and PCT expert representatives and two lay members. The PI and study coordinator are also members of the Steering Committee.

### Clinical analysis

The null hypothesis is that there will be no difference in primary outcomes between intervention and control patients. All data will be stored on a relational database, which will assist with ongoing management. Data will then be arranged for further analysis in other programs including Microsoft Excel^©^, GenStat and SPSS^©^. The patient population will be characterised using the appropriate descriptive statistics, with medicines categorised according to those described within the British National Formulary (BNF) and medical problems classified according to the World Health Organisation International Classification of Diseases (ICD-10). Descriptive analysis of pharmaceutical care issues and action points in intervention patients will be recorded.

In this paper we are restricting ourselves to a description of our primary analysis, which is a direct comparison of the two groups: intervention and control.

For the following outcome variables - number of falls, emergency hospital admissions and deaths - the total number of events in each care home will be aggregated, along with total resident days 'at risk' in the same period. The events data will be analysed by fitting a hierarchical generalized linear mixed model to them. The basic generalized linear model used will be a log-linear model with Poisson error and log ('at risk' days) as an offset. The care homes themselves will be represented as random effects. Fixed effects in the model will be the intervention itself, the home size (small, medium, large), and resident-type (a two-level factor: residential care vs nursing care). The fact that 'mixed' homes have both types of resident means that the event-counts and 'at risk' days counts will have to be aggregated separately for each type in these homes. The standard error associated with the estimate of the effect of the intervention will be adjusted as necessary to take account of the cluster design. These models will be fitted in the GenStat statistical package using residual maximum likelihood (REML).

It is to be noted that the above analyses are essentially at the level of the care home rather than the patient. There are no identified covariates for the primary analysis. However, exploratory analyses may be conducted at the patient level, should a case emerge for including patient-level covariates in a secondary analysis.

With respect to the study's second primary outcome variable measure (number of drugs which match the STOPP criteria for each patient at each time point), this will also be analysed using a generalized linear mixed model. In this case there is a strong candidate for a patient-level covariate, ie the number of drugs which match the STOPP criteria at baseline. This variable will be analysed at the patient-level, with the baseline covariate (ie the number of drugs which match the STOPP criteria at baseline). The basic generalized linear model here will use a negative binomial distribution for the error. The fixed and random effects will be as previously stated.

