## Methods

### Trial design

A cluster randomised controlled trial will be used and a flow chart outlining the study design appears in Figure 1. The project will involve care homes for older people (average age > 65 years) registered with a GP in the local area. Thirty care homes will be recruited to the trial: 15 in the intervention arm and 15 in the control arm. Intervention homes will receive a MMRS at baseline and six months, with final data collection at 12 months. Control homes will receive usual care (support they currently receive from the National Health Service (NHS)) with data collection at baseline and at 12 months. Following final data collection at the control homes, a MMRS can be implemented.

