### Allocation to treatment

Care homes will be segmented according to their resident mix (three categories: care home, care home with nursing, care home with residential and nursing beds) and size (i.e. number of beds - again three categories: small, medium and large). Recruitment will then proceed in 'waves'.

In the first wave a relatively homogeneous block of homes with approximately 30 residents will be approached as this represents the optimum number of residents for delivery of the intervention. For the second and subsequent waves, the homes to be approached will be decided purely on the basis of facilitating recruitment. For practical (i.e. workload) reasons, consenting homes will be allocated to intervention or control sequentially after consent is obtained using minimisation. This strategy has the advantage of achieving approximate balance between treatment groups with respect to stratifying factors (here resident mix and size) whilst allowing the practical advantage of being able to make allocations sequentially as homes are recruited, rather than having to wait for blocks to accumulate. Recruitment will cease once approximately 900 residents have been recruited.

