### Data collection

Data will be collected from intervention and control homes at three points (baseline, 6 months and 12 months) as follows. All patient demographic, medical history, medication details and falls data (in previous six months) will be obtained from records in the care home (i.e. individual care plans and accident books) and GP practices by a pharmacy technician one month prior to the planned care home visit in intervention homes. For the control homes, data collection at baseline will take place as soon as possible after allocation (within a month of allocation) and will be facilitated by the pharmacy technician. The data collected at this point will include patient demographic and falls data.

Details of all recommendations arising from the medication review, as well as implemented interventions, will be recorded for intervention homes. This process will be repeated after six months. After 12 months follow-up this data will again be extracted from care home records and GP practices (for intervention and control homes, with data collection for the latter encompassing the 6 month and 12 month points) by a pharmacy technician. Anonymised data will be passed to the research team for analysis.

For the economic evaluation, data will be collected on the time taken to develop and provide the intervention and on the resource items likely to change as a result of the intervention. Resource items will include visits to (and from) health care professionals (such as GP, nurse and dietician), as well as hospital and social services.

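### The primary falls model omits baseline falls although both arms record them: the test stays valid, but precision is given up and chance imbalance stays partly in the estimate

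*Protocol article*

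**What the plan says.** Under Clinical analysis, falls are aggregated by home (by resident type within mixed homes) and fitted with a "log-linear model with Poisson error and log ('at risk' days) as an offset" and a random effect for home. The fixed part is listed in full: "Fixed effects in the model will be the intervention itself, the home size (small, medium, large), and resident-type". The text then states: "There are no identified covariates for the primary analysis". Patient-level covariates are left to possible exploratory or secondary analyses.

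Under Data collection, baseline falls are obtained in both arms. The text leading to the intervention homes says: "All patient demographic, medical history, medication details and falls data (in previous six months) will be obtained from records in the care home". For control homes, baseline collection takes place within a month of allocation: "The data collected at this point will include patient demographic and falls data".

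The second primary outcome, the count of drugs matching STOPP, is treated differently: "In this case there is a strong candidate for a patient-level covariate, ie the number of drugs which match the STOPP criteria at baseline". That baseline goes into its model.

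The design is stated under Trial design: "Thirty care homes will be recruited to the trial: 15 in the intervention arm and 15 in the control arm". Under Allocation to treatment, the minimisation factors are resident mix and home size. Prior falls are not among them.

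**The concern.** Falls are the outcome on which the trial is sized. They come from each home's own care plans and accident books, so a home's rate reflects both its case mix and how fully it records. Either may carry over from the baseline period to follow-up, and the home's prior rate would pick up both. With only 30 homes, the arms can differ by chance in prior fall rate, and neither the minimisation nor the fitted model addresses that difference beyond what size and resident type explain.

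Two things are at stake. One is precision: the interval may be wider than the collected data allow. The other is the estimate in the trial actually run: if the arms differ in prior fall rate, part of that difference remains in the reported effect. If the term is added only after an imbalance has been seen, the choice is open to challenge as data-driven.

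**Working it through.** **Inputs from Sample size estimation:** variance 4 per patient over six months, target difference 0.49, ICC 0.02, 30 residents per home, 80% power, 5% significance (taken as two-sided). From Trial design: 15 homes per arm.

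**The plan's own figures.** 2 × ((1.96 + 0.84) × 2 / 0.49)² ≈ 261.5 per group (stated 261). Design effect 1 + 29 × 0.02 = 1.58. 261 × 1.58 = 412.4 per group, 824.8 in total (stated 412 and 824). These reproduce, and they use no baseline adjustment.

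**Variance of a home mean.** Between homes: 0.02 × 4 = 0.0800. Within homes: 0.98 × 4 / 30 = 0.1307. Total: 0.2107.

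**Chance imbalance in baseline falls.** SD of the difference between arms = √(2/15 × 0.2107) = 0.168 falls per resident per six months, or 34% of 0.49. This ignores any gain from minimising on size and mix.

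**Correlation of home means, baseline to follow-up.** Let c be the persistence of home effects and w the correlation over time of a resident's own counts within a home. Then

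r = (0.0800c + 0.1307w) / 0.2107

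Adjustment multiplies the variance of the treatment contrast by 1 − r². Power is Φ(2.80/√(1 − r²) − 1.96). The protocol gives neither c nor w, so both are assumed over a range. Where size and type are taken to explain half the home variance, 0.0800 becomes 0.0400 and the total becomes 0.1707. Unadjusted power is then already 87.5%, because 2.80 × √(0.2107/0.1707) = 3.11.

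| c | Home variance explained by size and type | w | r | Variance reduction | Power without → with baseline |
|---|---|---|---|---|---|
| 0.5 | half | 0 | 0.12 | 1.4% | 87.5% → 88% |
| 0.5 | none | 0 | 0.19 | 3.6% | 80% → 81% |
| 1 | half | 0 | 0.23 | 5.5% | 87.5% → 89% |
| 1 | none | 0 | 0.38 | 14% | 80% → 86% |
| 1 | none | 0.2 | 0.50 | 25% | 80% → 90% |
| 1 | none | 0.4 | 0.63 | 39% | 80% → 95% |

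**Carry-over of an imbalance.** A one-SD imbalance left unadjusted shifts the estimate by r × 0.168. That is 0.032 (about 6% of 0.49) at r = 0.19, 0.064 (13%) at r = 0.38 and 0.105 (about 21%) at r = 0.63.

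**Cost of the covariate.** A t-based check with 15 full homes of 30 per arm uses 25 degrees of freedom without the term and 24 with it. At r = 0.38, power goes from 80.2% to 85.8%, so the lost degree of freedom does not cancel the gain.

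All of this uses the protocol's normal approximation on six-month means, not the planned Poisson mixed model.

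**The case against.** The strongest reply is that this is a choice about efficiency, not an error. Allocation is by minimisation, homes are random effects and the standard error allows for clustering, so chance imbalance is already reflected in the interval. The sample size reaches its stated 80% without any baseline term. All of that stands: neither the validity of the test nor any power claim in the plan fails.

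The size of the gain is also uncertain. Size and resident type are minimised on and fitted, and may already absorb part of the home variance. Home effects may drift and residents turn over. This stands too, and it is why the table starts near 1%.

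A reader might infer that the plan forbids a baseline covariate. It says only that none is identified and leaves patient-level covariates open for secondary work. Omission from the primary model is the exact description. A reader might also infer that the plan contradicts itself, since STOPP gets its baseline. The STOPP analysis is at patient level and the text gives no precision or imbalance argument, so this is a difference in treatment with a context. That context does not explain the omission, however, because a home-level baseline rate fits the home-level model without any move to patient level.

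Two practical objections also hold. The log of a zero count is undefined, which could matter in small home-by-type cells. Control baseline data are extracted after allocation, and the six-month window is not repeated for them.

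**Conclusion.** The point holds as a worthwhile improvement to the primary falls analysis. The model as listed has no baseline falls term, the data for one are collected in both arms, and minimisation does not cover it. The loss is in precision, together with a partial shift in the estimate when the arms happen to differ in prior fall rate.

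The benefit ranges from almost nothing to substantial, depending on a correlation the protocol does not report. It is tempting to treat the 14% variance reduction and 86% power as a minimum. They are not: they require home effects that persist fully and of which size and type explain none. The 90–95% power figures further require resident-level correlations of 0.2–0.4, for which the protocol offers no source. Nor does an imbalance pass into the estimate in full; it does so only in proportion to r.

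The recommendation does not depend on where in the range the truth lies, because the cost is small throughout.

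**What to change.** Replace the sentence saying that no covariates are identified with a pre-specified fixed covariate in the home-level Poisson model: the home's (or, in mixed homes, the home-by-resident-type) baseline fall rate over the six months ending before allocation. Enter it on the log scale with a stated continuity correction for zero counts, or use an equivalent transform. State that the same window and the same record sources apply in both arms, since extraction from records takes place after allocation.

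The cost is a short change of wording and one degree of freedom. Baseline falls are already being collected, so the main addition is to fix the window for control homes. A resident-level negative binomial model with baseline falls, along the lines planned for STOPP, is an optional alternative. It would replace the stated home-level analysis and is not needed for this fix.

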### Economic analysis

The economic evaluation will estimate the cost-effectiveness of a MMRS in care homes for older people compared to usual care from a NHS health and personal social services perspective. Established and accepted economic methodologies will be employed throughout [31,32].

An incremental cost analysis will be undertaken. Resource items likely to change as a result of the intervention (as well as the cost of developing and providing the intervention) will be identified, measured and valued. Healthcare resource use data will be collected from care home and GP records. The base case will capture only those costs incurred by the NHS (including, for example, health care professionals' time and travel to medication reviews, patient visits with health care professionals, admissions to secondary care, and medication) and personal social services. Unit costs will be derived from national published data (for instance Curtis 2009 [33]) for the most recent price year available.

This study will undertake a cost-effectiveness analysis to address the technical efficiency question of how best to provide medication review services to older people living in care homes: by multi-professional teams or via GP care (usual care). Effectiveness will be measured in terms of the change in number of falls. If non-dominance occurs (that is if costs are greater and the intervention is more effective or if the intervention is cheaper and less effective) an incremental cost-effectiveness ratio (the ratio of additional cost divided by additional benefit) will be produced in terms of the incremental cost per fall prevented. The confidence region around the incremental cost effectiveness ratio will be estimated using appropriate statistical techniques. Since this economic evaluation is being undertaken alongside a cluster randomised trial the analysis needs to reflect the increased uncertainty of randomising clusters rather than individuals. A number of approaches have recently been proposed for this, with each found to generate similar findings [34]. The stochastic analysis will enable a cost effectiveness acceptability curve to be produced [35] illustrating the decision uncertainty, that is the probability that the MMRS in care homes for older people is cost-effective compared to usual care for a range of willingness to pay per fall prevented values. The timeframe for the economic analysis will be that of the trial period.

### Limitations

The MMRS has the potential to impact on a number of factors that are not being measured in this study, but are likely to be important for medicines management in care homes. For example, the MMRS provides a positive way for pharmacists to work with GPs and care home staff. The review meeting offers an opportunity for the professionals to build relationships and to achieve a greater understanding of their respective roles and responsibilities. The MMRS may also influence positively the medicines culture at the care home, by addressing generic issues in the management and administration of medicines. Further research could explore such factors perhaps utilising action research or other qualitative methodologies. The study is also not measuring the impact of the intervention on the generic health-related quality of life of residents.

## Discussion

In January 2010 the Department of Health issued a CAS Alert [31] calling for a safety review of all aspects of the provision of medication to older people in care homes. Alert (2010) 001 was issued following the publication of the Care Homes Use of Medicines (CHUMS) [32] study that identified a high prevalence of medication errors. The alert calls for an integrated approach to determine how medicines management in care homes might be improved.

This study is seeking to establish the effectiveness of a novel model of clinical medication review in care homes involving a multi-professional approach. It is the first study to undertake an examination of direct patient outcomes together with an economic evaluation. The clinical medication review is innovative in that it involves the pharmacist working in collaboration with GPs and care home staff.

The study also has novel approaches to recruitment and consent. Care homes are being recruited with the support and agreement of their GPs and consent for participation in the study is being sought from GPs and care home managers - and not individual residents. This is because the intervention is provided at the level of the care home (i.e. to all residents) as is standard practice for the MMT team when delivering this service. This approach has the advantage of simplifying the process of securing informed consent. However, it does mean that no additional information is obtained from care home residents and, as indicated above under limitations, the study does not measure the impact of the intervention on, for example, residents' health-related quality of life.

The MMRS is intended to deliver improvements in a number of areas, including the quality of prescribing, increased patient monitoring, better health outcomes, and a potential reduction in the number of medications prescribed. Such a service will contribute to optimising therapy, improving patient safety and minimising problems in the management of medicines at care homes.

## Abbreviations

A&E: (Accident and Emergency); BNF: (British National Formulary); CQC: (Care Quality Commission); GP: (General Practitioner); ICD: (International Classification of Diseases); MAR: (Medicines Administration Record); MMRS: (Multi-professional Medication Review Service); MMT: (Medicines Management Team); NCSC: (National Care Standards Commission); NHS: (National Health Service); PCT: (Primary Care Trust); PI: (Principal Investigator); RCT: (Randomised Controlled Trial); REML: (Residual Maximum Likelihood); STOPP: (Screening Tool of Older Persons Prescriptions);
